### Rehabilitation protocol

In this trial, “high-intensity mobilization” is operationally defined as achieving out-of-bed mobilization at the level of standing or higher (e.g., standing or stepping) at an earlier stage of ICU stay than would be feasible with conventional mobilization methods, facilitated by the use of an MPL.

The criteria for initiating and discontinuing rehabilitation will follow those established in our previous studies [22, 23]. The initial rehabilitation level will be determined through discussion among physicians, nurses, and physical therapists (Fig. 1). Rehabilitation sessions will be conducted daily and will follow a stepwise progression, with each session set at a higher intensity than the preceding session (Fig. 2). Following the initial successful achievement of sitting at the edge of the bed, patients will undergo early high-intensity rehabilitation (standing or higher) using a MPL. Our prior research demonstrated that the use of an MPL enables patients to achieve standing earlier than that achieved with standard care [22]. For patients who are capable of standing or higher-level mobilization without MPL support, the device will not be required. Thus, the purpose of this protocol is to create a cohort in which earlier and more intensive rehabilitation can be performed using the MPL. Rehabilitation with MPL will continue until patients are transferred from the ICU to the general ward.

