**Fig. 1 Fig1:**
[figure not shown]
ICU rehabilitation initiation and discontinuation criteria. The flowchart summarizes the criteria for initiating and discontinuing ICU rehabilitation.The left panel describes the physiological and safety requirements for rehabilitation initiation, including respiratory, circulatory, and neurological stability, as well as sedation and analgesic evaluation (RASS, NRS, and BPS). The right panel outlines discontinuation criteria such as neurological changes, respiratory or circulatory instability, uncontrolled pain, or device-related risks. When discontinuation criteria are met, rehabilitation should be paused and restarted at a lower intensity level once the patient’s condition stabilizes. Abbreviations: MI, myocardial infarction; BP, blood pressure; SAT, spontaneous awakening trial; SBT, spontaneous breathing trial; RASS, Richmond Agitation-Sedation Scale; NRS, numerical rating scale; BPS, behavioral pain scale

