**Fig. 2 Fig2:**
[figure not shown]
Stepwise ICU rehabilitation protocol. The rehabilitation program is divided into five progressive levels. Level 1 consists of MRC muscle strength and ROM exercises. Subsequent levels involve resistance training, heads-up positioning, sitting on the edge of the bed, and standing or walking using a mobile patient lift when necessary. Progression to the next level is permitted if the discontinuation criteria are not met; if the discontinuation criteria are met, rehabilitation is resumed at one level lower. Resistance training should be conducted for areas with an MRC score ≤ 3. Abbreviations: MRC, Medical Research Council; ROM, range of motion

Mobilization is delivered daily, including weekends. On weekdays, mobilization is led by physiotherapists; on weekends, mobilization at the predefined high-intensity level (standing or higher) is maintained by trained ICU nurses (and physicians when needed) using the mobile patient lift, following the same standardized protocol and safety criteria. This approach was used in our previous MPL study [22] and was feasible without a physiotherapist present on weekends. Mobilization will be performed twice daily and, when feasible, up to three times daily. The appropriate number of sessions will be determined through discussion among physicians and nurses, with adjustments made as needed.

In cases where the patient refuses mobilization, the response will depend on the underlying reason. If refusal is due to pain or fever, symptomatic treatment will be provided. If refusal is due to fatigue, the session will be rescheduled. If patients exhibit depressive symptoms and decline participation, staff will provide supportive listening and ensure that no coercion is applied. When clinically indicated, consultation with appropriate specialists (e.g., psychiatry or psychosomatic medicine) will be arranged according to standard clinical practice. However, the patient will be approached again, and if consent is obtained, mobilization will be performed.

The frequency and duration of each mobilization session will be routinely documented in the electronic medical records as part of standard ICU practice and will be extracted for analysis.

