### Interventions

The intervention in this study will not involve differences in the intensity or frequency of rehabilitation; the focus will be on modifying protein intake between the two groups. In the control group, nutritional support will target the lower limit of protein intake recommended in current guidelines (1.2 g/kg/day) [9, 10]. In contrast, participants in the intervention group will receive a higher protein intake of 1.8 g/kg/day. As described previously, both caloric and protein intake will be adjusted to remain within 100–110% of the prescribed targets. Although European Society for Clinical Nutrition and Metabolism guidelines suggest higher protein targets for selected populations, such as trauma or obese patients [9], the present trial is not designed to individualize protein prescription based on diagnostic subgroups, but rather to evaluate the effect of two predefined protein targets under standardized mobilization conditions. Randomization is expected to distribute such patient characteristics evenly between groups.

The core intervention period will continue from Day 3, when protocolized protein delivery is initiated, until ICU discharge, death, or the initiation of oral intake, whichever occurs first, for a maximum of 28 days from randomization. During this period, standardized high-intensity mobilization will be provided as part of routine ICU care to all eligible patients.

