### Data collection

Baseline characteristics will be collected at the start of the intervention, and will include demographic and clinical data: age, sex, body mass index, primary diagnosis, and comorbidities assessed using the Charlson Comorbidity Index [26]. Severity of illness will be measured using the Acute Physiology and Chronic Health Evaluation (APACHE) II score. Additional clinical variables will include the presence of acute kidney injury (AKI) according to the Kidney Disease: Improving Global Outcomes criteria [27], presence of diabetes, score on the Malnutrition Universal Screening Tool [28], and the presence of malnutrition defined by the Global Leadership Initiative on Malnutrition criteria [29]. Furthermore, body composition will be assessed at enrollment using a bioelectrical impedance analyzer (InBody BWA2.0S; InBody Japan, Tokyo, Japan) to determine parameters including skeletal muscle mass, skeletal muscle index, fat-free mass index, and phase angle. Baseline FIM scores will not be collected because most patients are unable to undergo functional assessment at ICU admission due to sedation, mechanical ventilation, or impaired consciousness. Therefore, FIM was assessed only at hospital discharge, consistent with the study objective of evaluating post-ICU functional recovery.

Nutritional data will include the number of days from admission to initiation of enteral nutrition, the number of days until the target protein dose was achieved, and the mean intake of caloric, protein, parenteral caloric, enteral caloric, parenteral amino acid, and enteral protein during the intervention period. These data will be analyzed separately for Days 0–1 and from Day 3 onward.

Rehabilitation-related data will include the number of days from admission to initiation of mobilization, number of days mobilization was performed, and the ICU Mobility Scale score at ICU discharge [30].

In addition, treatment-related data will include the use of renal replacement therapy, use of ECMO, and the duration of mechanical ventilation.

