Safety outcomes will include serum creatinine level at hospital discharge, maximum blood urea nitrogen level during the intervention, mean insulin use, and maximum blood glucose levels. In addition, mobilization-related safety outcomes will include accidental removal of tubes or devices, the number of mobilization sessions discontinued, and reasons for discontinuation (respiratory, circulatory, neurological, fatigue, or other causes). The schedule of enrolment, interventions, and assessments follows the SPIRIT 2025 guidelines (Fig. 3).

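### Mobilisation and metabolic safety are raw counts and maxima that ignore exposure, so they mix safety with survival, ICU stay and session frequency

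*Protocol article*

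**What the plan says.** All references are to the protocol article.

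- **Outcome, mobilisation safety.** The measures are accidental removal of tubes or devices and "the number of mobilization sessions discontinued, and reasons for discontinuation (respiratory, circulatory, neurological, fatigue, or other causes". No denominator is attached.
- **Outcome, metabolic safety.** Besides creatinine at hospital discharge, the list is "maximum blood urea nitrogen level during the intervention, mean insulin use, and maximum blood glucose levels". The period is named for BUN only. Glucose has no stated window, and insulin has no stated unit.
- **Interventions.** Protocolised protein delivery runs from Day 3 "until ICU discharge, death, or the initiation of oral intake, whichever occurs first, for a maximum of 28 days from randomization".
- **Rehabilitation protocol.** On duration: "Rehabilitation with MPL will continue until patients are transferred from the ICU to the general ward". On frequency: "Mobilization will be performed twice daily and, when feasible, up to three times daily". Physicians and nurses settle the number of sessions, and the section on blinding says that they cannot be blinded. The same section states that session frequency and duration are charted and will be extracted.
- **Data collection.** The rehabilitation variables include the "number of days mobilization was performed", with no link to the safety count.
- **Statistical analyses.** Continuous outcomes are compared by t-test or Mann–Whitney U test. The covariance analysis that includes exposure duration is a sensitivity analysis of the primary findings and is not extended to safety.
- **Outcome, deaths.** There are rules for the functional, strength and pain scores of patients who die, and none for the safety measures.

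**The concern.** A count of discontinued sessions grows with the number of sessions begun, and a maximum grows with the number of days observed. Both depend on how long a patient remains under observation. That time is fixed by ICU discharge, death, oral intake and staff decisions about frequency. ICU stay and mortality are themselves secondary outcomes, so the trial is designed to ask whether the drivers of exposure differ between arms.

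The plan recognises variable exposure for functional recovery (Statistical analyses; Discussion) but not for safety. The Background cites evidence that higher protein may be harmful in some settings, and there is no independent monitoring board. The safety comparison should therefore be readable by itself. As written, an arm difference could reflect exposure alone, and a real difference could be masked by it.

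**Working it through.** **The plan's own figures.** The protocol gives no number for any safety outcome, so there is none to reproduce. Every rate below is an assumption chosen to show the mechanism. Only the two to three sessions a day come from the document.

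**1. Discontinued sessions.** Let s be sessions per day, p the stop probability per session in survivors, q the proportion who die, 10 and 4 the exposure days in survivors and in patients who die, and m the ratio of per-session risk before death to that in survivors. The expected count per patient is

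s × p × [(1 − q) × 10 + q × 4 × m].

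Take s = 2, p = 0.05, q = 0.20 in one arm and 0.35 in the other. With m = 1:

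- Lower-death arm: 0.10 × (8.0 + 0.8) = 0.88, from 2 × 8.8 = 17.6 sessions, a rate of 0.050 per session.
- Higher-death arm: 0.10 × (6.5 + 1.4) = 0.79, from 2 × 7.9 = 15.8 sessions, a rate of 0.050 per session.
- Ratio of counts: 0.79 / 0.88 = 0.90, a 10% difference with identical risk per session.

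| m | Count, 20% deaths | Count, 35% deaths | Rate, 20% | Rate, 35% |
|---|---|---|---|---|
| 1 | 0.88 | 0.79 | 0.050 | 0.050 |
| 2 | 0.96 | 0.93 | 0.055 | 0.059 |
| 2.5 | 1.00 | 1.00 | 0.057 | 0.063 |
| 3 | 1.04 | 1.07 | 0.059 | 0.068 |

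The counts are equal when 10 = 4m, so m = 10/4 = 2.5. In this set-up that point depends only on the ratio of exposure days, not on the death proportions. At m = 2.5 the counts show nothing although the rates differ.

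**2. ICU stay and frequency.** Earlier ICU discharge acts in the same direction as earlier death. At s = 2 and p = 0.05, mean exposure of 8 days against 10 gives 2 × 0.05 × 8 = 0.80 against 1.00. Frequency alone can change the count by up to 3/2 = 1.5 times within the stated range, if one arm had two sessions a day throughout and the other three.

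**3. Maxima.** Assume independent normal daily values with the same mean and spread in everyone. The expected maximum, in within-patient SDs above the mean, is 1.03 over 4 days, 1.54 over 10 days and 1.98 over 26 days. Averaged over the same arms:

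- 20% deaths: 0.80 × 1.54 + 0.20 × 1.03 = 1.44.
- 35% deaths: 0.65 × 1.54 + 0.35 × 1.03 = 1.36.

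The arm difference is about 0.08 SD. It would be smaller or reversed if values rise before death.

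**The case against.** Several objections have force.

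- **Direction.** A reader might infer that the arm with earlier deaths will look safer. The documents do not support that. It requires deaths to differ by arm and risk before death not to offset the shorter exposure. Raised risk before death is plausible, because the Fig. 1 caption names neurological change and respiratory or circulatory instability among the reasons to stop. An arm that recovers faster would also look safer.
- **Size.** A patient with 6 days at two sessions a day has 12 sessions, and one with 20 days at two to three has 40 to 60. At a 5% risk that is 0.6 against 2.0 to 3.0 stops. A reader might infer a 3- to 5-fold distortion between arms, but this contrasts two patients. Randomisation and a shared mobilisation protocol make the likely arm difference much smaller.
- **Data.** It would be wrong to say that the denominator is not collected: session frequency is due for extraction. What is missing is its link to the safety count.
- **Reason codes.** The Fig. 1 caption lists "uncontrolled pain, or device-related risks" among the stop criteria, while the outcome codes name fatigue and leave pain to the residual category. A reader might infer a contradiction. The caption gives examples only and the figure is not shown, so no error is established.
- **Mean insulin use** is not a maximum and does not accumulate mechanically with days. Only its unit is open.
- **Place of the detail.** Offsets and windows are often left to an analysis plan. That is fair for model detail. The article does, however, state both the measures and the tests, and together they ignore exposure.
- **The rate is not neutral.** Sessions started is a post-randomisation quantity, and a count per randomised patient is a legitimate measure of burden. This stands, and it is why the rate should be added and not substituted.

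**Conclusion.** The point holds in a limited form. The stated counts and maxima, compared directly between arms, mix safety with exposure, and exposure depends on survival, ICU stay, oral intake and session frequency chosen by unblinded staff. The distortion can run either way. Under the assumptions above it is about 10% of the discontinuation count for deaths of 20% versus 35%. It disappears when risk before death is 2.5 times higher and reverses at 3 times. BUN is the clearest case among the maxima, since its window is explicitly the intervention period. For glucose the window is simply not given, so its ending at death or ICU discharge would be an inference. The matter affects how safety is read. It does not touch the primary outcome or the sample size, but the remedy is cheap enough that the change should be made.

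**What to change.** 1. Keep the per-patient counts of discontinued sessions and accidental removals. Add each per session started, compared by a count model with log(sessions) as offset and an allowance for between-patient overdispersion. Define a session started and state the counting period, since lift mobilisation runs to ICU transfer while the intervention period may end earlier at oral intake.
2. Summarise BUN and glucose over one early window from Day 3, of a length fixed in advance and the same for all, or as the mean daily maximum over intervention days. State the glucose window either way.
3. Express insulin per intervention day.
4. Present all of these beside mortality by arm.

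**Cost.** The wording of the outcomes and analysis changes. The session data are already due for extraction and BUN is monitored daily, so the added work is mainly linking sessions to events and extracting daily glucose values. No interim analysis is planned, so this can still be specified before the arms are compared. Two limits remain: sessions started is itself affected by what happens after randomisation, and a fixed window is still cut short by death. The new summaries therefore supplement the per-patient count.

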**Fig. 3 Fig3:**
[figure not shown]
SPIRIT figure: Schedule of enrolment, interventions, and assessments. The schedule of enrolment, interventions, and assessments follows the SPIRIT 2025 guidelines. Abbreviations: ICU, intensive care unit; FIM, Functional Independence Measure; FSS-ICU, Functional Status Score for the ICU; MRC, Medical Research Council; MMSE, Mini-Mental State Examination; BPI, Brief Pain Inventory

### Statistical analyses

After data collection is complete, continuous variables will be presented as mean ± SD or as median with interquartile range (IQR), and categorical variables as numbers with percentages. Baseline characteristics and study outcomes will be compared between groups using the Student’s t-test or Mann–Whitney *U* test for continuous variables, and the chi-square test or Fisher’s exact test for categorical variables. All outcome analyses will be conducted according to the intention-to-treat principle.

The primary analysis will compare outcomes between groups according to the intention-to-treat principle.

As a sensitivity analysis, analysis of covariance (ANCOVA) will be performed to explore the robustness of the primary findings to variability in intervention implementation. As the actual duration of high-protein nutrition and high-intensity mobilization may vary among participants despite randomization, these variables will be included as covariates to account for differences in intervention exposure rather than to adjust the primary treatment effect.

Covariates included in the ANCOVA will be pre-specified based on clinical relevance and trial design considerations, not selected in a data-driven manner. Importantly, these analyses are intended as exploratory sensitivity analyses to aid interpretation of the results and will not replace the primary intention-to-treat comparisons.

Furthermore, sensitivity analyses will be performed with adjustment for the presence of acute kidney injury and use of renal replacement therapy (RRT).

For all analyses, missing data will be addressed under the assumption of missing at random using multiple imputation. Given the possibility of non-random loss to follow-up after hospital discharge, sensitivity analyses exploring departures from the missing-at-random assumption (e.g., pattern-mixture or delta-adjustment approaches) will be conducted, and the extent and patterns of missingness will be reported. Variables related to missingness or outcomes—including group allocation, age, sex, Glasgow Coma Scale, ICU length of stay, and APACHE II score—will be incorporated in the imputation model. The specification of the imputation model will be informed by assessment of missing data patterns and inter-variable associations to ensure model adequacy. This approach will also be applied to post-discharge follow-up outcomes, including those assessed at 60 days, to account for missing data due to transfer or loss of contact.

Model assumptions for ANCOVA will be evaluated using standard diagnostic procedures, including inspection of residual distributions and assessment of homoscedasticity. If major violations are identified, appropriate transformations or robust alternatives will be considered and reported.

No interim analyses will be conducted. All statistical analyses will be performed using R (version 4.5.0), and all statistical tests will be two-sided. Statistical significance will be set at 0.05 across all analyses.

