### Outcome

The primary outcome will be the total motor domain score of FIM at hospital discharge. The FIM motor score at hospital discharge was selected as the primary outcome because it represents the earliest clinically stable time point at which the cumulative effects of ICU-based interventions can be meaningfully assessed. FIM at ICU discharge may be influenced by non-clinical factors such as bed availability and transfer policies, and may underestimate functional recovery due to ongoing critical illness and sedation effects. In contrast, longer-term follow-up after discharge is more susceptible to loss to follow-up and confounding by post-ICU rehabilitation and social factors. Therefore, assessment at hospital discharge was considered the most appropriate balance between clinical relevance, feasibility, and internal validity.

Secondary outcomes and their assessment time points will be as follows:At ICU discharge: Functional Status Score for the ICU [31], Medical Research Council (MRC) score, and ICU length of stay.At 14 days after ICU discharge: FIM motor, cognitive subscale of FIM (FIM cog), Mini-Mental State Examination (MMSE), body composition parameters, MRC score, and Brief Pain Inventory (BPI).At hospital discharge: MRC score, FIM cog, body composition parameters, BPI, length of hospital stay, and mortality.At 60 days after hospital discharge: FIM motor score, MRC score, FIM cog, MMSE score, body composition parameters, and BPI.

Follow-up at 60 days post-discharge will be conducted during an outpatient visit scheduled at the time of discharge. For patients who die or cannot be assessed owing to severe consciousness disturbance, the FIM motor and FIM cog will be recorded at their minimum values (13 and 5, respectively), the MRC score will be assigned as 0, and the BPI will be recorded as missing. For patients who die before hospital discharge, FIM scores will be assigned as the minimum possible values (motor score 13 and cognitive score 5). This approach reflects that death represents the worst possible functional outcome and ensures that mortality is appropriately incorporated into the analysis of functional recovery rather than treated as missing data.

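### The primary FIM motor comparison is unadjusted and its test is left open, which gives up precision that age, APACHE II and Charlson index, all collected, could recover

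*Protocol article*

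**What the plan says.** The Outcome section fixes the endpoint: "The primary outcome will be the total motor domain score of FIM at hospital discharge". Patients who die, or who cannot be assessed because of severely disturbed consciousness, are scored 13, the scale minimum.

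The Statistical analyses section names the tests: "Baseline characteristics and study outcomes will be compared between groups using the Student’s t-test or Mann–Whitney *U* test for continuous variables". Of the primary analysis it says only "The primary analysis will compare outcomes between groups according to the intention-to-treat principle". No covariate is named, and nothing says when the t-test applies and when the Mann–Whitney test does.

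The same section plans an ANCOVA whose named covariates are the durations of high-protein nutrition and of mobilization. Of these it says "these variables will be included as covariates to account for differences in intervention exposure rather than to adjust the primary treatment effect". It adds that "these analyses are intended as exploratory sensitivity analyses to aid interpretation of the results and will not replace the primary intention-to-treat comparisons". A further sensitivity analysis adjusts for acute kidney injury and renal replacement therapy.

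Under Data collection, age and the Charlson index are recorded at baseline, and "Severity of illness will be measured using the Acute Physiology and Chronic Health Evaluation (APACHE) II score". Baseline FIM is not recorded. The missing-data text lists age and APACHE II among the variables tied to missingness or outcome and puts them in the imputation model. APACHE II also appears as a subgroup factor. The Randomization section describes 1:1 allocation in variable blocks and names no stratification factor.

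**The concern.** In a trial of 90 patients with no baseline value of the outcome and no named stratification factor, a prespecified baseline adjustment is the cheapest way to narrow the interval around the treatment effect. The plan collects suitable covariates and treats two of them as related to missingness or outcome when imputing, but does not use them in estimating the effect. The planned ANCOVA does not fill the gap: the covariates it names are exposure durations that arise after randomization, and it is labelled exploratory.

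The open choice of test adds to this. The t-test targets a difference in means, and the Mann–Whitney test a rank-based comparison. With deaths placed at the floor of 13, the choice between them is likely to arise. The plan also applies multiple imputation to all analyses. Rubin's rules pool an estimate and its standard error, and the Mann–Whitney test supplies no mean difference with a standard error to pool.

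At stake are the width of the primary confidence interval and the clarity of what is being estimated.

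**Working it through.** **Inputs from the protocol article (Sample size estimation).** SD 20, difference 17, two-sided α 0.05, 37 per group, 90 in total after 15% dropout. The 0.95 printed as β has to be read as power, since 80% power would need 22 per group and 90% would need 30.

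**Assumed inputs.** R² of 0.1, 0.2 and 0.3 for age, APACHE II and Charlson index together, and SDs of 25 and 30 as alternatives to 20. The documents give none of these values.

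**Step 1: the plan's own figure.** By the normal approximation, n = 2 × (1.960 + 1.645)² × (20/17)² = 35.97, so 36 per group. With the noncentral t distribution for an unadjusted t-test, n = 37 and power is 0.950. Dropout: 74/0.85 = 87.1, so 88 with equal arms, which 90 covers. The stated size is reproduced, and it belongs to the unadjusted comparison.

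**Step 2: the effect of adjustment.** Residual SD = SD × √(1 − R²). Standard error = residual SD × √(2/37). Equivalent sample-size factor = 1/(1 − R²). Power uses the noncentral t with 72 degrees of freedom unadjusted and 69 with three covariates.

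| R² | Residual SD (SD 20) | SE | 95% CI half-width | Sample-size factor | Power, SD 20 | Power, SD 25 | Power, SD 30 |
|---|---|---|---|---|---|---|---|
| 0 | 20.00 | 4.65 | 9.27 | 1.00 | 0.950 | 0.823 | 0.672 |
| 0.1 | 18.97 | 4.41 | 8.80 | 1.11 | 0.967 | 0.860 | 0.717 |
| 0.2 | 17.89 | 4.16 | 8.30 | 1.25 | 0.981 | 0.897 | 0.766 |
| 0.3 | 16.73 | 3.89 | 7.76 | 1.43 | 0.991 | 0.931 | 0.819 |

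Power is for a 17-point difference with 37 per group.

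**Step 3: chance imbalance.** With 45 per arm, the probability that a given covariate differs between arms by more than 0.2 SD is 2 × (1 − Φ(0.2/√(2/45))) = 0.343. If one covariate alone explained 30% of the variance, a 0.2 SD imbalance in it would move the estimated difference by √0.3 × 0.2 × 20 = 2.2 points, against the 17 points planned for.

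**The case against.** The strongest reply is that nothing here is an error. An unadjusted two-sample test is valid under randomization, it is the analysis for which the trial was sized, and covariate lists and test-selection rules are often left to an analysis plan, which may exist but is not shown. The first two parts stand. The third stands only in part: the article does not leave the primary analysis open to adjustment, because it names two unadjusted tests and says that the ANCOVA will not replace the primary comparison.

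It can also be said that adjustment is not wholly absent. Acute kidney injury and renal replacement therapy are adjusted for in a sensitivity analysis, and the ANCOVA covariates are to be prespecified on clinical grounds, which does not rule out age or severity. That is fair, but these analyses are secondary and none is stated to include the three covariates.

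A reader might infer stronger points that the documents do not support:

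- *Power is already below what is stated.* Step 1 gives 0.950 at the plan's own inputs. The sample size section says that variability could plausibly be larger, but also that the direction and size of any difference are uncertain.
- *Nothing in the design limits prognostic variation.* The Participants section requires independence in daily activities before admission and excludes several groups, including patients with neuromuscular disease. This restriction may also lower the R² left to recover.
- *The covariates are known to be strong predictors.* The article says only that age and APACHE II are related to missingness or outcome, and does not say even that of the Charlson index.
- *Chance imbalance undermines the result.* The Interventions section says "Randomization is expected to distribute such patient characteristics evenly between groups". In any one trial of this size that need not hold, but the unadjusted standard error and type I error already allow for chance imbalance.

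**Conclusion.** The point holds as a recommended improvement and not as a failure of validity. The plan fixes an unadjusted primary comparison, leaves two tests with different targets in play, and states no treatment effect adjusted for age, APACHE II and Charlson index.

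The gain forgone is a standard error about 5% to 16% smaller for an assumed R² of 0.1 to 0.3. If SD 20 holds, the practical effect is a narrower interval more than a better chance of detecting 17 points, because power is already 0.950. The power gain becomes material only if the SD is larger, as the SD 25 and SD 30 columns show. The direction of the gain is secure if the covariates are prognostic to the degree assumed. Its size rests wholly on an R² that the documents do not supply.

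**What to change.** Make the primary analysis one prespecified linear model of FIM motor score at hospital discharge on arm, age, APACHE II and Charlson index. Use heteroscedasticity-robust standard errors, and pool by Rubin's rules where values are imputed. Deaths and patients unassessable because of disturbed consciousness already carry the value 13, so they need no imputation for this outcome.

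Report the unadjusted difference in means alongside. Name either the Mann–Whitney test or a proportional-odds model as the sensitivity analysis for the floor at 13, so that the test is no longer chosen after the data are seen.

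The cost is three degrees of freedom, a change of wording and a few lines of analysis code. No further data are needed. The Trial status section reports that no participant had been enrolled when the manuscript was submitted. The change should be dated and documented before outcomes are examined by arm.
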